## Abstract

**Background::**

Gastrointestinal malignant tumors are the most common malignant tumors in elderly people in China, resulting in an increasing trend of morbidity and mortality. We conducted a non-randomized controlled trial to compare the effect of enhanced recovery after surgery (ERAS) versus Routine care on clinical outcomes in elderly patients after colorectal cancer surgery.

**Methods::**

This is a single center, non-random, parallel-controlled clinical trial, 60 patients aged ≥65 years will be randomized for Case group ERAS and Control group (routine care).

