## Introduction

1

The incidence rate and mortality rate of colorectal cancer in China are increasing year by year. Affected by diet and environment, the number of patients with rectal cancer has been high in China so that a large number of surgical treatments in hospital every year. Besides, the disease is also the main cause of death and a major public health problem as the number of patients is the second only to lung cancer and gastric cancer in China. It was estimated that 191,000 people died in 2015.^[1,2]^

With the improvement of living standard, the proportion of the elderly over 65 years old is increasing. Gastrointestinal cancer is the most common malignant tumor in the elderly over 75 years old in China, according to statistics, the annual incidence of colorectal cancer in the elderly over 75 years old in China is about 78,200. At the same time, with the progress of anesthesia technology, the number of elderly people who can receive surgical treatment has increased significantly.^[3,4]^ However, elderly patients with colorectal cancer after surgery are more likely to have adverse postoperative consequences, such as longer hospital stay, the occurrence of various complications, high readmission rate, etc, and the economic costs will be correspondingly high.^[5,6]^ Consequently, we present this research to prove the use of enhanced post-operative recovery (ERAS) which could reduce the adverse consequences of elderly patients after surgery, and improve the rehabilitation effect compared with routine care.

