### Trial design

2.1

This will be a non-random control trail with single center experience. Elderly patients will be included from the Affiliated Hospital of Southwest Medical University. We developed this protocol based on the 2013 statement of standardized protocol interventions: recommendations for intervention trials (SPIRIT).^[10]^Figure 1 shows the schedule for registration, assessment, intervention, and follow-up in accordance with spirit guidelines.

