### Data collection

2.4

We will collect the relevant indicators based on the final outcomes. The research assistant will collect the following data:

Basic information:

Age, gender, education level, body mass index, pathological type, and stage of cancer, ASA score of anesthesia, preoperative albumin, and globulin level.

Stress response indicators: Fasting blood glucose, C-reactive protein (CRP)

Immune function index: T lymphocyte subsets (CD3 +, CD4 +, CD8 +, CD4 + / CD8 +) and immunoglobulin (IgG, IgM, IGA)

Psychological assessment: Zung's self-rating Anxiety Scale (SAS) was used to evaluate the anxiety of the 2 groups

Postoperative recovery index and Economics: Anal exhaust time, first fluid intake time, total hospitalization time, total hospitalization expenses, gastric tube indwelling time and urinary catheter indwelling time

Postoperative complications: Anastomotic leakage, intestinal obstruction, pulmonary infection, urinary tract infection, urinary retention, wound infection.

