### Statistical analysis

2.11

In this study, the sample size was estimated by comparing 2 independent samples. Considering the loss of follow-up, the sample size was increased by 10%, so the final sample size (N1 + N2) ∗ (1 + 10%) was 110. Therefore, 55 patients in the case group and 55 patients in the control were selected in this study. SPSS 22.0 statistical software was used for data entry and statistical analysis (*P* < .05 was statistically significant). Statistical description was used for general data, ANOVA of repeated measurement was used for quantitative data, and rank sum test was used for rank data.

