## Discussion

3

ERAS is a process of improving the condition of surgical patients based on evidence-based nursing. The implementation of strengthening postoperative recovery can greatly improve the clinical effect and reduce the cost, making eras an important standard of surgical value-based nursing.^[13]^ An article summarizes the ERAS results of elderly patients (≥65 years) after colorectal surgery. The median overall incidence rate is 23.5%, the median postoperative loss is 6 days, and the overall postoperative complication rate quite high. Conducting this review shows that it is challenging to compare postoperative complications between studies, and the exclusion criteria are different, because there is no uniform way to define or evaluate complications. Many studies only evaluate selected complications or range of complications by organ system. Patients receiving ERAS require lower upfront costs than traditional caregivers. However, the evaluation results of this study should be based on the long-term results and functional results of patient treatment, so the overall cost-effectiveness has not been fully determined, and longer follow-up data is required for further research. This review compare ERAS with routine care, in which primary outcomes including the degree of pain relief, the length of the first exhaustion, the time of the first meal, Length of stay, and the incidence of complications would report. In this study, we want to evaluate the clinical effect of ERAS and traditional care in elderly patients with colorectal cancer surgery through retrospective analysis of the results and risk factors for postoperative complications.

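### The abstract says patients will be randomized in a trial that it and section 2.1 declare non-random, and no text shown says how a patient enters either arm

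*Protocol article*

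**What the plan says.** The Protocol article describes allocation in three places.

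- Abstract, Background: "We conducted a non-randomized controlled trial to compare the effect of enhanced recovery after surgery (ERAS) versus Routine care".
- Abstract, Methods: "non-random, parallel-controlled clinical trial, 60 patients aged ≥65 years will be randomized".
- Section 2.1, Trial design: "This will be a non-random control trail with single center experience".

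Section 2.11 (Statistical analysis) mentions how the groups are formed but gives no rule: "55 patients in the case group and 55 patients in the control were selected in this study".

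Two other statements bear on what may be concluded. The Introduction gives the aim as "we present this research to prove the use of enhanced post-operative recovery (ERAS) which could reduce the adverse consequences". The Discussion says that ERAS and traditional care will be compared "through retrospective analysis of the results and risk factors for postoperative complications".

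**The concern.** How patients reach the two arms is the basic design fact of a controlled trial. Under random allocation, a difference between arms beyond chance can be attributed to the intervention. Under non-random allocation, it may also reflect who was chosen for which arm. The analysis then has to deal with confounding, and the conclusion has to be worded accordingly.

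The abstract asserts both. It is the most widely read part of the article, so a reader or systematic reviewer could class the study as a randomised trial when its design section says otherwise. The Introduction's aim of proving the benefit of ERAS goes further than a non-randomised comparison of this size can support.

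**Working it through.** The point rests on wording, so the check is to compare the statements.

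**Allocation**

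| Place | Label |
|---|---|
| Abstract, Background | non-randomized |
| Abstract, Methods, first half of the sentence | non-random |
| Abstract, Methods, second half of the same sentence | will be randomized |
| Section 2.1 | non-random |
| Section 2.11 | groups selected; no rule |

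Non-random appears three times, including in the formal design section. Randomized, as a description of this trial, appears once, as a verb. The text shown describes no sequence, concealment or randomisation step, and no non-random rule either (such as surgeon's choice, ward, calendar period or patient preference). The contradiction therefore cannot be resolved from the document. The flow chart (Figure 2) is not shown, and nothing here relies on its content.

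**Direction of the study**

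Section 2.1 plans inclusion of patients. Section 2.4 says "The research assistant will collect the following data". Section 2.5 plans extra blood samples on day 1 after surgery, and sections 2.5 and 2.6 plan assessment until 30 days after surgery. All of this is prospective. The Discussion's retrospective analysis does not fit it.

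**Illustration of what is at stake**

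The document gives no figure for imbalance between the arms, so the following rests on assumptions.

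- Group size: section 2.11 inflates by 10% to 110, so the base is 110 / 1.10 = 100, or n = 50 per group.
- Assumed: no true effect; a normally distributed outcome compared by a two-sample t-test at two-sided 0.05; a prognostic imbalance favouring ERAS of b = 0.1, 0.2 or 0.3 SD.
- Noncentrality = b × √(n/2), with √(50/2) = 5. This gives 0.5, 1.0 and 1.5.
- With 98 degrees of freedom the critical value is 1.984. The probability that a noncentral t exceeds it is about 7%, 17% and 32%. With b = 0 it is 2.5%.
- The abstract gives 60 patients, not 110, which is a separate inconsistency. With 30 per group, √(30/2) = 3.873, the noncentralities are 0.387, 0.775 and 1.162, and the probabilities are 5.7%, 11.5% and 20.7%.

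The pattern is the same at either sample size. These figures show how unadjusted selection can look like benefit. They do not estimate the bias in this trial.

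**The case against.** The strongest reply is that *randomized* is a slip, probably of translation, for *assigned*. Three statements agree on non-random, and an article may leave allocation detail to the full protocol. The first part is plausible and largely stands: the labels are not evenly balanced, and non-random is the likelier intention. The second part also stands in that the missing rule alone would not be a finding. It matters here because the article does state the allocation method, in two incompatible ways, and nothing in the text decides between them. If it is a slip, the abstract claims a stronger design than the trial has.

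A reader might infer that there are three rival designs: random, non-random and retrospective. The document does not support that. The Discussion applies *retrospective* to the analysis of results and risk factors, not to allocation or enrolment, and the paragraph is garbled: it also refers to the study as a review. It is a secondary wording error.

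A reader might also infer that fitter patients will in fact be steered to ERAS, or that the trial ought to be converted to randomised allocation. Nothing shown gives evidence of steering, and running both arms at one hospital does not show that randomisation is feasible.

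The wording about proof is also softer than it first looks. The Introduction says ERAS could reduce adverse consequences. It later speaks of analysing effectiveness and safety, and the abstract speaks of helping to evaluate them. The aim still needs aligning, but it is a supporting point.

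**Conclusion.** The concern holds in this form: the abstract's Methods sentence contradicts itself, the abstract's Background and section 2.1 on whether patients are randomised, and the text shown does not say how a patient enters either arm. The finding follows from the wording alone and needs no assumption. It must be corrected because allocation determines which analysis is valid and whether a causal conclusion is allowed.

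The bias figures (about 7%, 17% and 32% with 50 per group) depend wholly on assumed imbalances of 0.1 to 0.3 SD and on a t-test that section 2.11 does not name. They carry no weight in judging how serious the error is. Section 2.11 names no adjustment for confounding, but an analysis plan that is not shown may contain one, so that is context and not a separate defect.

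**What to change.** If the trial is non-random, as section 2.1 states:

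1. In the abstract's Methods sentence, replace *randomized* with *assigned*.
2. State in section 2.1 the rule by which a patient enters each arm.
3. Reword the aim in the Introduction so that conclusions are limited to a non-randomised comparison open to selection bias, and drop the language of proof.
4. State that the comparison is adjusted for prespecified baseline variables already collected under section 2.4, such as age, ASA score, cancer stage and albumin. If the analysis plan already does this, refer to it.

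If patients are in fact randomised, correct the non-random labels in the abstract's Background, the abstract's Methods and section 2.1 instead, and state the method of randomisation.

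In either case, remove the reference to retrospective analysis from the Discussion.

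The cost is small. Items 1 to 3 are text changes. Item 4 adds a model to the analysis but no new data collection. Converting the trial to concealed random allocation would strengthen it, but that is an optional change of the declared design and is not needed to correct this error.

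### The abstract gives a total of 60 patients, section 2.11 gives 110 (55 per group), and nothing in the protocol reconciles the two

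*Protocol article*

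**What the plan says.** The abstract, under Methods, gives the size of the trial in one sentence: "60 patients aged ≥65 years will be randomized for Case group ERAS and Control group (routine care"). Both groups are named, so the 60 reads as the whole trial. The abstract does not say how the 60 divide between the groups.

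Section 2.11 (Statistical analysis) gives the size again, this time with a derivation. It says that "the sample size was estimated by comparing 2 independent samples". It then allows for attrition ("Considering the loss of follow-up, the sample size was increased by 10" per cent) and concludes: "so the final sample size (N1 + N2) ∗ (1 + 10%) was 110". The group sizes follow: "55 patients in the case group and 55 patients in the control were selected in this study".

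Section 2.11 names no outcome, effect size, standard deviation, event rate, power or sidedness for this calculation. The 0.05 significance level is stated for the analysis. Section 2.9 (Withdrawal and dropout) says that there will be no interim analysis.

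**The concern.** A trial has one recruitment target, and here the same document gives two that differ by nearly a factor of two. Both are current text, and neither belongs to a list of superseded changes.

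The target decides when recruitment stops and what size of effect the trial can be expected to detect. If the two figures stand, staff working from the abstract and staff working from section 2.11 would stop at different points. A later reader could not tell whether a trial that ended with 60 patients had finished as planned or had stopped early. A reader of the abstract alone would also take the trial to be about 55% of the size that its own calculation asks for.

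**Working it through.** **Inputs**
- Abstract, Methods: total 60, split not stated.
- Section 2.11: final total 110; groups of 55 and 55; increase for loss to follow-up 10%, applied as (N1 + N2) × (1 + 0.10).
- Section 2.11: significance level 0.05, sidedness not stated.
- Not stated anywhere: effect size, standard deviation or rates, power, and the outcome behind the calculation.

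**Step 1. Does the 110 agree with its own formula?**
- Base before the increase: 110 / 1.10 = 100, so 50 per group at equal allocation. This 100 is back-calculated; it is not printed.
- Forward: (50 + 50) × 1.10 = 110 = 55 + 55.

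The stated rule was applied correctly. The base of 100 itself cannot be reproduced, because its inputs are not given.

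**Step 2. Can the 60 be any quantity in that calculation?**

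| Reading of 60 | Figure it would have to match | Match? |
|---|---|---|
| Final total | 110 | No, 50 short (60/110 = 55%) |
| Total before the increase | 100 | No, 40 short |
| Base to be inflated | 60 × 1.10 = 66, against 110 | No |
| Size of one group | 50 or 55 | No; 60 per group would make 120 |
| Number at an interim look | Section 2.9 excludes interim analysis | No |
| Pilot stage or evaluable subset | Not described anywhere | No support |

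No reading fits.

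**Step 3. Illustration of what 60 would mean, on assumed inputs**

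Assume a continuous outcome, two-sided alpha 0.05, equal groups, and a design with 80% power at 50 per group. With 60 enrolled there are 30 per group. After 10% loss there are 30 × 0.9 = 27.

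Normal approximation:
- Standardised difference: d = (1.960 + 0.842) × √(2/50) = 2.802 × 0.2 = 0.560.
- Power at n per group: Φ(d × √(n/2) − 1.960).
- n = 30: Φ(0.560 × 3.873 − 1.960) = Φ(0.21) = 58%.
- n = 27: Φ(0.560 × 3.674 − 1.960) = Φ(0.10) = 54%.

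The noncentral t distribution gives d = 0.566, and power of 57.7% and 53.2%.

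Range over other assumptions (normal approximation):

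| Assumed design at 50 per group | Power at 30 per group | Power at 27 per group |
|---|---|---|
| 80%, two-sided 0.05 | 58% | 54% |
| 90%, two-sided 0.05 | 71% | 66% |
| 80%, one-sided 0.05 | 61% | 57% |
| 90%, one-sided 0.05 | 73% | 69% |

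Steps 1 and 2 use only figures in the document or arithmetic on them. Step 3 does not, and the finding does not depend on it.

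**The case against.** The strongest case on the other side accepts that the two totals conflict but limits what follows from it.

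- **The 60 may be a drafting slip.** If so, the trial is being run to 110 and the only harm is a misleading abstract. This stands: the shortfall is real only if 60 is the operative target, and the document does not say which figure is.
- **The power figures are not the protocol's.** Section 2.7 (Study outcomes) includes the incidence of complications, which is a proportion. Section 2.11 plans repeated-measures ANOVA and rank-sum tests, and no outcome is tied to the sample size. A difference in standard deviations may not be the relevant scale, and the 30 + 30 split is also assumed. This stands too. A reader might infer that the trial is known to have only 53% to 58% power, but the document does not support that. It supports only the statement that 60 is below 110 and below the implied 100.
- **The 110 is only partly derived.** Its base cannot be reproduced, so a reader who takes 110 as proven correct goes too far. It is the likelier figure because it alone carries a formula and group sizes.
- **The inflation rule.** A reader might add that 110 is itself wrong, because dividing by 0.9 gives 100/0.9 = 111.1, or 112 in two equal groups. The section states its rule openly and applies it correctly, and the difference is two patients. It is not part of this point.

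The flow chart (Figure 2) was not available for this review. Whatever it shows, the two sentences in the text would still disagree. Nor does an article's brevity explain the conflict: the size is not left to a fuller document but stated twice with different values.

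**Conclusion.** The contradiction holds and needs no outside input: 60 in the abstract against 110 (55 + 55) in section 2.11, a gap of 50 patients that no other text resolves. It is an inconsistency between two stated totals, not a mistake in the calculation.

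The consequence is conditional. If 60 were the operative target, the trial would be 50 patients short of its final figure and 40 short of the implied figure before the increase, whatever the unstated inputs were. How much power that would cost is unknown; the percentages in the working show only the order of magnitude under the stated assumptions. If 110 is operative, the abstract misstates the trial's size and nothing else changes.

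It must be corrected either way, because the recruitment target is a basic design figure.

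**What to change.** Confirm the true recruitment target and state the same number in the abstract and in section 2.11.

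- **If 110 is the target (the likelier case):** change the abstract to 110 patients (55 per group). The cost is one line of text.
- **If 60 is the target:** replace the 110 and the 55 + 55 in section 2.11, and give a new sample-size justification for 60 from the sponsor's own inputs: the outcome, the assumed effect and variability or rates, the power and the sidedness. The illustrative figures above should not be copied into the protocol. The cost is a rewritten justification and a less favourable stated precision.

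Figure 2 should be checked against whichever number is confirmed.

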**Results::**

This study will help to evaluate the clinical feasibility, safety and effectiveness of ERAS in elderly patients undergoing colorectal resection compared with routine care.

**Protocol registration number::**

ChiCTR2000034984

## Introduction

1

The incidence rate and mortality rate of colorectal cancer in China are increasing year by year. Affected by diet and environment, the number of patients with rectal cancer has been high in China so that a large number of surgical treatments in hospital every year. Besides, the disease is also the main cause of death and a major public health problem as the number of patients is the second only to lung cancer and gastric cancer in China. It was estimated that 191,000 people died in 2015.^[1,2]^

With the improvement of living standard, the proportion of the elderly over 65 years old is increasing. Gastrointestinal cancer is the most common malignant tumor in the elderly over 75 years old in China, according to statistics, the annual incidence of colorectal cancer in the elderly over 75 years old in China is about 78,200. At the same time, with the progress of anesthesia technology, the number of elderly people who can receive surgical treatment has increased significantly.^[3,4]^ However, elderly patients with colorectal cancer after surgery are more likely to have adverse postoperative consequences, such as longer hospital stay, the occurrence of various complications, high readmission rate, etc, and the economic costs will be correspondingly high.^[5,6]^ Consequently, we present this research to prove the use of enhanced post-operative recovery (ERAS) which could reduce the adverse consequences of elderly patients after surgery, and improve the rehabilitation effect compared with routine care.

The surgical team has developed and implemented multidisciplinary care programs, included ERAS, which improves patient outcomes and reduces hospital stay.^[6,7]^ ERAS includes evidence-based changes in traditional care, such as consultation before admission, avoiding mechanical bowel preparation, shortening fasting, carbohydrate drinks for 2 hours before surgery, avoiding fluid overload, minimally invasive surgery, avoiding early removal of drainage tubes, and catheters, and multimodality of opioid retention analgesia, early feeding and activities. In 1 meta-analysis, ERAS during colorectal surgery was significantly associated with the reduction of postoperative complications, total hospital costs, and early recovery of gastrointestinal function, without increasing 30 day readmission or mortality.^[8]^ Another study showed satisfactory short-term clinical results and demonstrated that laparoscopic D2 lymphadenectomy combined with era is safe and feasible.^[7]^ ERAS is widely accepted to be the gold standard for the treatment of colorectal disease in patients.^[8,9]^ However, there are few articles on the elderly. Our study intends to analyze the effectiveness and safety of clinical application of ERAS in elderly patients with colorectal cancer, and to observe its impact on postoperative recovery of elderly patients with colorectal cancer.

